### Data collection methods

#### Quantitative process evaluation

Table 2 provides an overview of the outcomes measured for the quantitative part of the process evaluation, including the populations targeted by these measurements. The outcomes were chosen based on the logic model underlying this study (Fig. 3). Therefore, data on five major outcome domains will be collected (highlighted in bold numbers in Fig. 3): (1) implementation strategies and activities, (2) implementation of the *interprof* ACT intervention package (as a whole and single components), (3) key elements of interprofessional collaboration, (4) further domains related to interprofessional collaboration and medical care, and (5) contextual factors. The major outcome domains (1) to (4) relate to the assumed change mechanisms (intermediate outcomes), while the major outcome domain (5) reflects potentially relevant moderators. Each of these major domains comprises multiple domains and, in some cases, additional subdomains, which are measured in terms of different dimensions such as attitudes, dose and reach, adaptations, current practice, or self-reported quality and satisfaction.

**Table 2 Tab2:** Overview of outcome domains and subdomains of the quantitative process evaluation

Domains	Subdomains	Dimensions	Target population and measurement points						Measurement instruments (existing tools used^**a**^)
			IPAVs	RNs	NHDs	NHRs	GPs	STM	
**Implementation strategies and activities**									
Implementation strategies	Kick-off meeting	Attitudes, quality, and satisfaction	(T0b)	(T0b)	(T0b)	(T0b)	(T0b)	(T0b)	Questionnaires, minutes
	IPAV characteristics	E.g., roles and self-efficacy	T0b	–	–	–	–	T0b	Questionnaires, minutes
	IPAV training	Duration, adaptations, quality, and satisfaction	T0b	–	–	–	–	T0b	Questionnaires, minutes
	IPAV supervision	Quality and satisfaction	T0b	–	–	–	–	T0b	Questionnaires, minutes
IPAV work	Collaboration IPAV and IPAV substitutes	Quality and satisfaction	T1, T2	–	–	–	–	–	Questionnaires
	IPAV activities, e.g., in-house training courses and discussions with target groups	Current practice	T1, T2	–	–	–	–	T1, T2	Questionnaires
Implementational work within team (normalization process theory)	Coherence, cognitive participation, collective action, reflexive monitoring	–	T1, T2	T2	–	–	–	–	Questionnaires (NoMAD questionnaire)
***interprof*** **ACT intervention package**									
Intervention package as a whole	–	Dose and reach	T1, T2	–	–	–	–	–	Questionnaires (NoMAD questionnaire), minutes
Name badges		Choice and adaptation, dose and reach, local policies, current practice	T1, T2	T0a, T2	T0a, T2	–	T0a, T2	T1, T2	CRF, questionnaire, minutes
Mandatory availability rules	–	Choice and adaptation, dose and reach, attitudes, current practice, quality, and satisfaction	T1, T2	T0a, T2	T0a, T2	–	T0a, T2	T1, T2	CRF, questionnaire, minutes (Koverdem, InDemA)
Designated contact persons		Choice and adaptation, dose and reach, attitudes, local policies, current practice, quality and satisfaction	T1, T2	T0a, T2	T0a, T2	–	T0a, T2	T1, T2	CRF, questionnaire, minutes (InDemA)
Standardized home visits		Choice and adaptation, dose and reach, attitudes, current practice, quality, and satisfaction	T1, T2	T0a, T2	T0a, T2	T0a, T2	T0a, T2	T1, T2	CRF, questionnaire, minutes (InDemA)
Pro re nata medication		Choice and adaptation, dose and reach, current practice, quality and satisfaction	T1, T2	T0a, T2	T0a, T2	–	T0a, T2	T1, T2	CRF, questionnaires, minutes
Shared goal setting		Choice and adaptation, dose and reach, attitudes, current practice, quality, and satisfaction	T1, T2	T0a, T2	T0a, T2	–	T0a, T2	T1, T2	CRF, questionnaire, minutes (InDemA, Koverdem, PSAT)
**Key elements of interprofessional collaboration**									
Interprofessional communication		Attitudes, current practice, quality, and satisfaction	T1, T2	T0a, T2	T0a, T2	–	T0a, T2	–	CRF, questionnaires (CPAT, Koverdem)
Involvement of NHR		Current practice, quality, and satisfaction	T2	T0a, T2	T0a, T2	T0a, T2	T0a, T2	–	CRF, questionnaires (ZAP)
Contribution of involved professions		Attitudes, current practice, quality, and satisfaction	T1, T2	T0a, T2	–	–	T0a, T2	–	Questionnaires (CPAT, InDemA, Jefferson Scale, PSAT)
Coordination of care decision and care planning		Attitudes, current practice	–	T0a, T2	T0a, T2	–	T0a, T2	–	CRF, questionnaires (InDemA)
**Further domains related to interprofessional collaboration and medical care**									
General interprofessional collaboration		Attitudes, quality and satisfaction, time resources	T1, T2	T0a, T2	T0a, T2	–	T0a, T2	–	CRF, questionnaires (InDemA, Koverdem)
General (medical) care for NHR		Quality and satisfaction utilization of emergency or hospital services (self-reported changes), adverse outcomes	T2	T2	T2	T0a, T2	T2	–	CRF, questionnaires (ZAP, EUROPEP)
Further outcomes		Staff outcome, marketing outcome	–	–	T0a, T2	–	–	–	CRF
**Contextual factors**									
Meso: organizational level	Time resources		T1, T2	–	–	–	–	–	Minutes
	Leadership and work environment		T1, T2	T2	T0a, T2	–	–	–	Questionnaires (PES Nursing Work Index, NoMAD), minutes
	Financial and staff resources		T1, T2	T0a, T2	T0a, T2	–	T0a, T2	–	CRF, questionnaires, minutes
	Structures of collaboration and medical care	Attitudes, current practice, quality, and satisfaction	T1, T2	T0a, T2	T0a, T2	–	T0a, T2	–	Questionnaires (InDemA adapted)
	GP office and NH characteristics		–	–	T0a, T2	–	T0a, T2	–	CRF, questionnaires (Koverdem), minutes
Micro: staff level	Sociodemographic characteristics of all persons involved in implementation		T0b	T0a, (T0b), T2	–	–	T0a, (T0b), T2	T0a, (T0b)	Questionnaires, minutes
	Expected effects of high quality RN-GP collaboration		–	T0a, T2	T0a, T2	–	T0a, T2	–	CRF, questionnaires (Koverdem)
	Competences of RNs, GPs, and IPAV		T2	T0a, T2	T0a, T2	–	T0a, T2	–	CRF, questionnaires (Koverdem), minutes
Micro: NHR level	Utilization of GP office (formal characteristics)		–	–	–	T0a, T2	–	–	Questionnaires (ZAP)
	Family involvement in medical care		–	–	–	T0a, T2	–	–	Questionnaires (Koverdem)
Multiple levels	Unmet implementation support needs (IPAV)		T1, T2	–	–	–	–	–	Questionnaires
	Other factors (open-ended questions)		T0b, T1, T2	T0a, T2	T0a, T2	–	T0a, T2	T1, T2	Questionnaires, minutes

Instruments: Zufriedenheit in der Arztpraxis (“Satisfaction in GPs office”, ZAP) [25]. Survey instruments of the research project “Optimization of the cooperation between general practitioners and home care services” Koverdem [26]. Measures of the European Project on Patient Evaluation of General Practice Care (EUROPEP) [27]. Measures of interprofessional collaboration designed for the pre-post evaluation study “Interdisciplinary Implementation of Quality Instruments for the Care of residents with Dementia in Nursing Homes” (InDemA) [28]. Normalization Measure Development QUES (NoMAD) [29, 30]. Partnership Self-Assessment Tool (PSAT) [31]. Jefferson Scale of Attitudes toward Physician–Nurse Collaboration [32]. Collaborative Practice Assessment Tool (CPAT) [33]. Practice Environment Scale of the Nursing Work Index (PES-NWI) [34, 35]

*Abbreviations*: *CRF* case report form, *GPs* general practitioners, *IPAVs interprof* ACT agents, *NHD* nursing home directors, *NHRs* nursing home residents, *T0a* before randomization, *T0b* after randomization, *(T0b)* as participants and moderator of kick-off meeting, *T1* follow-up after 6 months, *T2* follow-up after 12 months, *RNs* registered nurses, *STM* study team member

^a^Single items or subscales of reported tools are used for the outcome domains in question. In addition, self-developed items are used for the measurement of all outcome domains

The major outcome domain “implementation strategies and activities” includes various dimensions (e.g., quality and satisfaction) of the implementation of the kick-off meetings and the IPAV training and the IPAV supervision. These dimensions will be assessed from the perspectives of the groups targeted by these implementation strategies (e.g., participants of the kick-off meetings, IPAVs) and those responsible for the application of these implementation strategies (e.g., study team members). Data will be gathered by means of semistructured minutes and questionnaires consisting of self-developed items. In addition, information will be collected on the activities undertaken by the IPAVs and the nursing staff to implement the *interprof* ACT interventions. This information will be collected from the IPAVs, RNs, and the study team members by means of standardized questionnaires consisting of self-developed items and items of the Normalization Measure Development (NoMAD) questionnaire [29, 30]. This instrument measures the core constructs of the Normalization Process Theory (NPT), i.e., coherence, cognitive participation, collective action, and reflexive monitoring, which describe and explain critical mechanisms of successful implementation of new complex interventions into the routines of healthcare practice [36, 37]. These constructs emphasize the continuous activities undertaken by involved persons both individually and collectively to make the new intervention meaningful, usable, and useful for their practice, to adapt novel and existing practices to each other and to evaluate and reflect on noticeable effects [36]. The convergent and structural validity and the reliability of the NoMAD questionnaire have been confirmed in several surveys among health professionals [29, 30, 38]. For this process evaluation, items reflecting all four NPT core constructs were chosen from the German version of the NoMAD questionnaire [39] and adapted to the terminology of the *interprof* ACT intervention package (Additional file 2).

The major outcome domain “implementation of the *interprof* ACT intervention package” contains several domains and subdomains to measure the success of the implementation activities in terms of the following dimensions: dose and reach of the intervention package as a whole and of the individual *interprof* ACT interventions, adaptations made to the single interventions, and attitudes and subjectively experienced quality with regard to these interventions. Adaptations made to the *interprof* ACT interventions will be recorded by study team members by completing semistructured minutes of the kick-off meetings and the supervision encounters as well as by IPAVs (questionnaires at T1 and T2). Dose and reach are directly measured by repeated 10-step global judgments of the IPAVs on the degree of implementation (1 = not implemented, 10 = fully implemented). The judgments of IPAVs, RNs, nursing home directors, GPs, and NHRs on attitudes, current practices and/or subjectively experienced quality of/satisfaction regarding *interprof* ACT interventions will provide an indication of the fidelity and quality of the implementation. Respective judgments will be collected at T0 and T2 by means of standardized questionnaires comprising self-developed items and items of existing measurement instruments with established psychometric performance [26, 28–31] (Table 2 and Additional file 2).

Two other major domains, “key elements of interprofessional collaboration” and “further domains related to interprofessional collaboration and medical care,” address the key elements of interprofessional collaboration (e.g., interprofessional communication, involvement of NHRs, contribution of involved professions), additional aspects of collaboration and experiences of quality of care assumed to be influenced by the *interprof* ACT intervention package (Fig. 3). These outcomes will be assessed in terms of attitudes, current practice, and subjectively experienced quality or satisfaction from various perspectives (IPAVs, RNs, nursing home directors, GPs, and NHRs) at different measurement points (T0, T2). Standardized questionnaires consisting of self-developed items and items of established measurement tools [25–28, 31–33] will be used (Table 2 and Additional file 2).

The contextual factors (major outcome domain (5)) comprise domains and subdomains that relate to attributes of the health system, the involved organizations, the *interprof* ACT intervention package, the staff, and the NHRs, which are assumed to have moderating effects on implementation success, interprofessional collaboration, and the quality of medical care for NHRs (Fig. 3). Following the underlying evidence [15], they are classified as factors at the macro-, meso-, and microlevels. Data on these domains and subdomains will be collected from each target group that contains or is affected by the contextual factors of interest. To gather these data, standardized questionnaires, case report forms, and semistructured minutes of supervision encounters will be used. Whenever justified and possible, items of validated measurement tools [26, 29, 30, 34, 35] will be integrated into these data collection instruments, complemented by self-reported items (Table 2 and Additional file 2).

The questionnaires and minute templates were designed based on existing measurement tools used in previous process evaluation studies on complex interventions to improve the quality of care in long-term institutions [8, 40]. The questionnaires for the RNs and GPs consist of two parts: one general part (part A) containing items to be answered independently of collaboration with a certain GP (questionnaires for the RNs) or a certain nursing home (questionnaires for the GPs) and a specific part (part B) that contains items specifically referring to collaboration with a certain GP’s office (questionnaires for the RNs) or a certain nursing home (questionnaires for the GPs). The items of the general part A cover all major outcome domains but do not include items on current practice and the subjectively experienced quality of/satisfaction with interprofessional collaboration and medical care within the major outcome domains “implementation of *interprof* ACT intervention package” and “key elements of interprofessional collaboration.” Additionally, part A does not include items referring to contextual factors that are specific to one collaborating GP office or nursing home (e.g., staff competencies in this institution). Respective outcomes are assessed specifically by part B of the questionnaires for GPs and RNs. Here, GPs are asked to complete a part B questionnaire specifically for each nursing home in which they provide medical care for NHRs participating in this trial. This means that the questionnaires for the GPs include as many parts B as the number of participating nursing homes with which they are currently collaborating. In contrast, the questionnaires for the RNs include specific part B questionnaires only for a 30% random sample of the GPs’ offices currently responsible for medical care for participating NHRs in their nursing home. This approach is used to avoid a large number of part B questionnaires being completed by RNs in nursing homes collaborating with more than six GPs’ offices [8].

Questionnaires for the RNs and GPs were piloted before the T0 measurements by means of cognitive interviews with nursing staff (*n* = 8) of 3 nursing homes and 10 GPs not involved in the main study. Within this pilot study, the completeness and comprehensibility of the questionnaires were assessed, and the relevance of the items of the major outcome domain “key elements of interprofessional collaboration” was determined by means of the content validity index. The pilot study revealed only minor need for revision of the questionnaires. Based on these findings, single items were deleted, added, or rewritten.

All questionnaires are paper-based. The questionnaires for the RNs, IPAVs, and GPs will be completed by the target persons. Participating GPs will receive postal questionnaires together with prepaid opaque return envelopes. Questionnaires for RNs and IPAVs will be directly handed to them by study team members during scheduled follow-up visits. Anonymously completed questionnaires will be collected by the study team members (IPAV questionnaires) or NHD (RN questionnaires). Questionnaires for NHRs will be part of structured oral interviews conducted by study team members for the collection of patient-reported data for the main trial at follow-up visits T0 and T2 [12].

#### Qualitative process evaluation

Data collection for the qualitative part comprises non-participating observations and semistructured interviews. Table 3 presents an overview of the themes considered in interviews and observations.

**Table 3 Tab3:** Overview of themes considered in interviews and observations of the qualitative process evaluation

Data collection method	Themes
Semistructured interviews	• Process sequences of care, interprofessional collaboration, and hospital admission • Everyday work context of GPs and RNs • Perception of work processes between GPs and RNs • Barriers and facilitators for process performance • Evaluation of process changes through *interprof* ACT intervention (only in IG) • Barriers and facilitators for implementation of *interprof* ACT measures (only in IG) • Feasibility of *interprof* ACT measures (only in IG)
Non-participating observations	• Communication and interaction between participants during kick-off meeting (only in IG) • Tailoring of *interprof* ACT measures during kick-off meeting (only in IG) • Process sequences of care, interprofessional collaboration, and hospital admission • Communication between GPs and RNs • Barriers and facilitators for implementation of *interprof* ACT measures (only in IG) • Evaluation of process changes through *interprof* ACT measures (only in IG) • Feasibility of *interprof* ACT measures (only in IG)

*Abbreviations*: *GPs* general practitioners, *IG* intervention group, *NHRs* nursing home residents

For the observations, one or two researchers will visit each of the eight participating nursing homes at T0, T1, and T2 to observe GP-RN interaction and communication as well as the implementation of the *interprof* ACT intervention and associated work process changes in the intervention group. Short conversations with GPs and RNs will be held before or after the observations if possible. The participation of NHRs is not intended but may be considered in relevant situations of communication between GPs, RNs, and NHRs. In addition to these observations, one researcher will attend the kick-off meetings to observe the interaction and communication between GPs and RNs when choosing and tailoring *interprof* ACT intervention components. Observations will be carried out with semistructured observational guidelines [41]. The observers will appear explicitly as scientists, and there will be no active participation of observers in the situation [42]. Observers will take notes while observing. The notes will be pseudonymized and then stored in a word processor (e.g., Microsoft Word).

In addition to the non-participating observations, interviews will be conducted with GPs and RNs. These interviews complement the observation data for the description of the care process and the evaluation of process changes through the *interprof* ACT intervention package in the intervention group. Furthermore, they serve to clarify observations and assess respondents’ perceptions of the processes. Semistructured interview guidance will be developed by the researcher team consisting of open questions that allow an unbiased and flexible approach. Interviews will be conducted by one interviewer with one respondent at a time. Interviews will take place in the nursing homes or at any other place chosen by the interview partners. Interviews will be audio-recorded and subsequently transcribed and pseudonymized. If the interview partners prefer that the interview will not be recorded, the interviewer will take notes. During the data collection process, the research team will regularly discuss the initial findings and adjust the interview guidelines to account for emerging themes.

For observations, an overall time frame of 1 to 3 days at 1 to 3 h a day per nursing home per measurement point is expected. Approximately four interviews involving one or two GPs and two RNs are planned per nursing home per measuring point.

### Data management

Study data in the process evaluation will be recorded both pseudonymized (Nursing or facility directors, NHRs) and anonymized (RNs, GPs, IPAVS, and study team members). For pseudonymized data, the personal data of the study participants will be kept separately from the study data. A retrospective correlation to a person is only possible with the help of a “key” which is maintained in the study center. The data will be entered into the electronic database according to the four-eye principle. The paper-based data is stored in the participating study centers and electronically in the database on a server. To ensure data quality, a plausibility check of the data will be carried out by an independent monitor. All original data will be stored for 10 years and destroyed afterwards. Generally, all data will be handled according to current data protection law.

### Data analysis

Data will be analyzed in a stepwise manner. First, quantitative and qualitative data will be analyzed independently from each other, followed by iterative triangulation. All analyses will be explorative, framed by the underlying logical model (Fig. 3). Statistical analyses will be performed using IBM SPSS Statistics (version 20) and Microsoft Excel. Software packages of MAXQDA (VERBI GmbH) and SAP Signavio will be used to facilitate the management, analysis, and visualization of qualitative data.

#### Quantitative data

To answer the three research questions of the quantitative process evaluation, data on outcome domains for each measurement point will be analyzed by means of descriptive statistics: frequencies (proportions) in the case of categorical variables and measures of location (mean and median) and dispersion (standard deviation (SD) and interquartile range (IQR)) in the case of ordinal or continuous variables. If psychometrically justified, items referring to the same outcome subdomain or dimension will be summarized into one sum score. Only items using the same answer scale will be considered for this aggregation, and the structural validity and reliability will be tested by means of exploratory factor analyses (principal component analysis) and Cronbach’s alpha. Newly created sum-scores will be maintained if each item loads with an eigenvalue of ≥0.25 on the one factor assumed a priori and/or the Cronbach’s alpha is above 0.4. These thresholds are specifically defined for the purpose of this study, taking statistical conventions for estimation and interpretation of these measures into account [43] and assuming that in many cases, not more than five items will be eligible for combination into one sum score.

Initially, all quantitative data will be analyzed and aggregated at the cluster (i.e., nursing home) level. For this aggregation, a two-step approach will be used. First, the direction and size of changes over time will be descriptively estimated for single items or subscales. For the assessment of pre-post changes (T0 versus T2), the difference between the two mean or median values will be estimated. Following the effect size Cohen’s *d* [44], a mean difference with a size of ≥20% of the standard deviation across study groups will be interpreted as a relevant change or difference. For median values, a median difference of 0.5 in case of ≤5-step scales or 1.0 in case of >5-step scales will be regarded as relevant. Change estimates will be classified as follows: relevant changes in the favorable direction reflect positive changes, relevant changes in the nonfavorable direction reflect negative changes, and nonrelevant changes are interpreted as indifferent effects (no changes). Some items will be assessed only at the T2 follow-up visit to directly measure the subjectively perceived degree of change in certain collaboration or care procedures. For these items, the size of the change will be classified based on the distance between the estimated mean value and the most neutral value of the scale. If the mean value is higher (positive values) or lower (negative values), the distance between 20% of the pooled standard deviation and the most scale-neutral value, a relevant change will be assumed, either positive or negative, depending on the direction. In other cases, the mean values will be regarded as being indifferent.

Second, the change estimates across items and subscales will be aggregated by means of vote counting, i.e., the number of positive and negative changes and indifferent findings will be counted and visually depicted in tables for single-outcome subdomains or dimensions. Vote counting findings from each perspective (NHRs, NHDs, RNs, IPAVs, GPs) will be summarized per nursing home in tables (intervention group only), and nursing homes will then be ranked with regard to their degree of implementation achieved for each *interprof* ACT component. Based on this ranking, nursing homes will be inspected for differences in contextual factors. These findings will then inform the triangulation of qualitative and quantitative data and the subsequent creation of a preliminary model to answer the second research question, i.e., the impact of the degree of implementation on the quality of interprofessional collaboration, taking moderating effects of potentially relevant contextual factors into account.

Furthermore, for the outcome domains “implementation of the *interprof* ACT intervention package,” “key elements of interprofessional collaboration,” and “further domains related to interprofessional collaboration and medical care,” the vote counting findings per nursing home will be visually compared between the intervention and control groups to explore between-group differences in the changes in attitudes and current practice and the quality of RN-GP collaboration.

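### Raw sum scores are judged by fixed median cut-offs, so from the second item upward the bar for a relevant change falls as a scale gets longer

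*Protocol article*

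**What the plan says.** All of this stands in the protocol article, Data analysis, Quantitative data.

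- Scoring: if psychometrically justified, "items referring to the same outcome subdomain or dimension will be summarized into one sum score". The restriction is "Only items using the same answer scale will be considered for this aggregation", and the authors expect that in many cases "not more than five items will be eligible for combination into one sum score". Division by the number of items is not mentioned.
- What is judged: "the direction and size of changes over time will be descriptively estimated for single items or subscales". Single items and multi-item scores fall under the same rules.
- Which statistic: "the difference between the two mean or median values will be estimated". The article does not say when the mean and when the median is used.
- Mean rule: "a mean difference with a size of ≥20% of the standard deviation across study groups will be interpreted as a relevant change or difference".
- Median rule: "a median difference of 0.5 in case of ≤5-step scales or 1.0 in case of >5-step scales will be regarded as relevant".

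The resulting classes (positive, negative, no change) are vote-counted per subdomain or dimension. They are used to rank intervention homes on implementation and compared visually between the study groups, and they inform the later regression model.

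**The concern.** The median cut-offs are in raw points and depend only on whether the scale has more than five steps. A sum score's range grows with every item, but its cut-off stays at 1.0. The mean rule is expressed in standard deviations and has no such problem, so the two rules treat the same score differently.

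A vote from a five-item scale then needs a much smaller shift per item than a vote from a two-item scale. Vote counting assumes that votes are exchangeable. If strictness depends on how many items survived the psychometric check, the counts, the ranking of homes and the visual comparison partly reflect scale length.

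**Working it through.** **No figure to reproduce.** The cut-offs are set, not derived, and the article reports no formal sample size estimation.

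**Inputs from the article.** Raw sums; cut-offs of 0.5 and 1.0; usually at most five items per sum; on average four RNs reached per home (Table 1).

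**Assumptions.** Items have five steps, coded 1–5; the article gives a step count only for the IPAVs' 10-step global judgment. Category shares are 7/18/35/27/13%, which gives an item SD of 1.1. The inter-item correlation r is 0.3–0.5 on the latent scale. The T0 and T2 respondents are independent. Ten respondents per wave is an illustrative middle value. Eighteen is an upper bound for residents: 210 GPs × 3 residents / 34 homes = 18.5.

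**Step 1: the bar by number of items.** A sum of k five-step items has 4k + 1 possible values and range 4k. Two items already give 9 steps, so the cut-off is 1.0 for every k ≥ 2.

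| Items k | Cut-off | Share of range | Points per item |
|---|---|---|---|
| 1 | 0.5 | 0.5/4 = 12.5% | 0.50 |
| 2 | 1.0 | 1/8 = 12.5% | 0.50 |
| 3 | 1.0 | 1/12 = 8.3% | 0.33 |
| 4 | 1.0 | 1/16 = 6.3% | 0.25 |
| 5 | 1.0 | 1/20 = 5.0% | 0.20 |

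If the steps are meant to be those of the item's own answer scale, the cut-off is 0.5 for every k. The bar then falls further, to 0.5/20 = 2.5% of the range at five items. With 10-step items it falls from 1/9 = 11.1% to 1/45 = 2.2%.

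**Step 2: how often a home without true change is called relevant.** Monte Carlo, 100,000 homes per setting. The ranges cover r = 0.3 to 0.5. A single item is judged by 0.5, a sum by 1.0 and an item mean by 0.5.

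| Respondents per wave | 1 item | Sum of 2 | Sum of 3 | Sum of 4 | Sum of 5 | Mean of 5 items |
|---|---|---|---|---|---|---|
| 4 | 78% | 59–62% | 69–72% | 75–78% | 79–82% | 42–50% |
| 10 | 62% | 46–48% | 57–61% | 65–69% | 70–75% | 25–33% |
| 18 | 45% | 39–41% | 48–52% | 56–61% | 63–67% | 13–20% |

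At two items the sum and the item mean are the same test (1.0/2 = 0.5), so both start from the same rate. After that the sum's rate rises and the item mean's rate falls.

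**Step 3: comparison with the mean rule.** For five items, the 0.2 SD rule labels 77–80% of no-change homes at 4 respondents, about 64% at 10 and about 56% at 18.

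**Step 4: cut-offs in SD units at five items.** The simulated SD of the sum is 3.56 (r = 0.3) to 4.13 (r = 0.5).

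- The 1.0 cut-off on the sum is 1.0/4.13 = 0.24 to 1.0/3.56 = 0.28 SD.
- A 0.5 cut-off on the item mean equals 2.5 points on the sum: 2.5/4.13 = 0.61 to 2.5/3.56 = 0.70 SD.

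**The case against.** Several points on the other side stand.

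- **It is not every added item.** For five-step items, going from one item to two also doubles the cut-off, so the share of range is unchanged and false labels fall (78% to 59–62% at four respondents). A reader might infer that combining items always raises false labels. The figures do not support that: with four respondents, sums of two or three items do better than a single item, four is about neutral, and five adds 1–4 points.
- **Few respondents explain much of the noise.** The scale-free mean rule also mislabels most no-change homes at four respondents. Against that rule, the excess from five-item sums under the median rule is at most about 11 points. The wider gap to item means arises largely because 0.5 on an item mean is a stricter bar.
- **The scope is limited.** Only sums judged by medians are affected, and the article leaves the choice of statistic open. Dose and reach are measured directly by single global IPAV judgments. All analyses are declared explorative, and the rule is the same in every home and both groups, so it adds noise and non-comparability rather than bias towards one group.

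A reader might also infer that a blank item lowers a sum and turns a home to negative change. The article does not support this. It states no rule for blank items, and such handling is commonly left to an analysis plan. The result would need a blank at T2 counted as zero on an item where higher is better; a blank at T0 would push the other way.

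None of this removes the mismatch itself, which follows from the stated rules by arithmetic.

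**Conclusion.** The concern holds for multi-item scores judged by medians. As written, a raw sum meets a cut-off that ignores item number, so for five-step items the bar falls from 12.5% of the range at two items to 5.0% at five. Votes from subdomains with different numbers of items are then not comparable, although they are counted and ranked as if they were.

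The arithmetic depends only on the five-step assumption, and other readings of the step count give the same direction or a steeper fall. The false-label rates also depend on the assumed item SD, correlation and respondent numbers. At 10 or 18 respondents the rise with scale length is clear; at four, sample size dominates. The documents do not support a claim that sum scoring is the main source of false labels, or that it favours one study group. The point is worth correcting because the labels feed the ranking and the later model, and the correction is short.

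**What to change.** State one rule for multi-item scales. Either option removes the dependence of the raw-point bar on item count:

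1. Score each retained scale as the mean of its items on their common answer scale, and apply the median cut-off that belongs to that answer scale. The existing same-answer-scale condition makes this possible. The bar is then 0.50 points per item, or 12.5% of the range, for any number of five-step items.
2. Keep the sums, but judge multi-item scales only by the 0.2 SD mean rule already in the article.

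Either costs one sentence and some re-scoring or re-labelling; under Trial status, analysis is ongoing. Option 1 has a real downside: at five items its bar is about 0.6–0.7 SD, roughly three times the mean-rule threshold, so some smaller true changes would be classed as no change. Option 2 avoids that but still labels 77–80% of no-change homes at four respondents for a five-item scale. Neither option cures the noise from few respondents per home, so vote tables should show the number of respondents behind each vote.
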